# Efficacy of intra-articular hypertonic dextrose prolotherapy versus normal saline for knee osteoarthritis: a protocol for a triple-blinded randomized controlled trial

**DOI:** 10.1186/s12906-018-2226-5

**Published:** 2018-05-15

**Keywords:** Dextrose prolotherapy, Normal saline, Randomized controlled trial, Knee osteoarthritis, Study protocol

## Abstract

**Background:**

Knee Osteoarthritis (KOA) is a very common condition with prevalence rising with age. It is a major contributor to global disability and has a large socioeconomic burden worldwide. Conservative therapies have marginal effectiveness, and surgery is reserved for severe symptomatic KOA. Dextrose Prolotherapy (DPT) is an evidence-based injection-based therapy for chronic musculoskeletal conditions including KOA. The standard “whole joint” injection method includes intra-articular injection and multiple extra-articular injections at soft tissue bony attachments. The procedure is painful and requires intensive procedural training often unavailable in conventional medical education, which potentially limits access. Intra-articular injection offers the possibility of a less painful, more accessible treatment. The aim of this project is to assess the clinical efficacy of intra-articular injection of DPT versus normal saline (NS) for KOA.

**Method:**

Seventy-six participants with KOA will be recruited from the community. We will conduct a single center, parallel group, superiority randomized controlled trial comparing DPT and NS injections, with blinding of physician, participants, outcome assessors and statisticians. Each group will receive injections at week 0, 4, 8 and 16. The primary outcome will be the Western Ontario McMaster University Osteoarthritis Index pain scale (WOMAC), and secondary outcomes include WOMAC composite score, the WOMAC function and stiffness subscale, the Visual Analogue Score of pain, objective physical function tests (the 30 s chair stand, 40- m fast paced walk test, the Timed up and go test) and the EuroQol-5D (EQ-5D). All outcomes will be evaluated at baseline, and 16, 26 and 52 weeks. All analyses will be conducted on an intention-to-treat basis using linear mixed regression models.

**Discussion:**

This paper presents the rationale, design, method and operational aspects of the trial. The findings will determine whether IA DPT, an inexpensive and simple injection, is a safe and effective non-surgical option for KOA. The results can be translated directly to clinical practice, with potentially substantial impact to patient care.

**Trial registration:**

The trial (ChiCTR-IPC-15006617) is registered under Chinese Clinical Trials Registry on 17^th^ June 2015.

## Background

Knee osteoarthritis (KOA) is a common chronic arthritis leading to joint pain and disability worldwide [1]. KOA is age-related [2]; by age 65, around 30% of the population has osteoarthritis [3, 4]. KOA is an expensive disease with significant socioeconomic burden due to its high prevalence, worker absenteeism and costly health care utilization [5, 6]. While exercise and weight reduction are effective in KOA, factors such as fatigue, accessibility and the arthritis itself have been identified as barriers for the actual participation [7]. Other conservative therapies such as physiotherapy, oral analgesic medications and complementary therapies such as acupuncture and herbal treatment have marginal effectiveness [8–11]. Total knee replacement (TKR) for advanced KOA is effective but costly [12].Thus, a safe and effective treatment option that complements the current conservative therapy remains a top priority in clinical practice and research [13, 14].

Pain and functional impairment in KOA are associated with a multifactorial set of degenerative intra-articular cartilage, bone and synovial knee structures, in addition to a complex interaction between genetic, biochemical, biomechanical, psychosocial, and other factors such as neurogenic inflammation and central pain sensitization [15–17]. The heterogeneous pain mechanisms in KOA may explain the variable responses to different therapies, and the search for effective non-surgical treatment for KOA has been challenging.

Dextrose prolotherapy (DPT) is an injection-based therapy for chronic musculoskeletal pain conditions including KOA [18]. The mechanism of action is likely multifactorial, and is hypothesized to work through stimulation of fibroblast and vascular proliferation, dense collagen deposition, and cartilage growth [19]. Additionally, dextrose solutions may have potential sensorineural analgesic effects as suggested recently by the effect of epidural injection of dextrose in the treatment of chronic non-surgical low back pain [20]. DPT may therefore treat KOA by targeting structural dysfunction, reducing nociceptive drive and minimizing peripheral sensitization.

The standard injection method of DPT involves a whole joint injection, consists of single intra-articular joint injection and multiple extra-articular injections at soft tissue attachments [21]. Pain and functional improvement in KOA have been reported in randomized controlled trials [22, 23], systematic review [24, 25] and meta-analysis [26, 27]. However, the procedure is painful due to multiple skin punctures, and premedication with a centrally acting opioid analgesic is sometimes used. In addition, the extra-articular injection protocol requires additional intensive postgraduate training, the access to which may be limited, minimizing availability of DPT.

The beneficial effects of a protocol using serial intra-articular dextrose injections have been reported in a small number of studies, though the results are limited by small sample size, lack of control arm or modest study design [28–32]. The current project aims to conduct a rigorous randomized controlled trial (RCT) to evaluate the intra-articular approach of DPT for KOA.

The primary aim of this study is to assess the clinical efficacy of intra-articular DPT versus normal saline (NS) in terms of self-reported knee pain at 52 weeks. We hypothesize that DPT is superior to NS in pain reduction as assessed by the Western Ontario McMaster University Osteoarthritis Index (WOMAC), a guideline recommended validated self-reported outcome in KOA trials [33]. Our secondary aims are to assess the clinical efficacy of intra-articular DPT versus NS in terms of subjective and objective functional improvement and quality of life at 52 weeks, using the WOMAC functional scale, 30 s chair stand, 40 m fast paced walk test, the Timed up and go test and EuroQuol-5D. EuroQuol-5D [34, 35].

## Methods

### Study Design

The study is a 52-week, two-arm, parallel, superiority randomized controlled trial aimed to evaluate the comparative effectiveness of DPT versus NS for KOA. The study design follows the recommendation from the Osteoarthritis Research Society International (OARSI) [33], and the reporting will follow the Standard Protocol Items: Recommendations for Interventional Trials (SPIRIT) [36]. The study has been approved by the Joint Chinese University of Hong Kong – New Territories East Cluster Clinical Research Ethics Committee.(CREC no. 2014.059). This trial has been prospectively registered in the Chinese Clinical Trial Registry on 17^th^ June 2015. (Registration no. ChiCTR-IPC-15006617) The study workflow is summarized in Fig. 1.

**Fig. 1 Fig1:**
[figure not shown]
Study flow chart

### Eligibility

Eligibility will be screened by a trained research assistant using a phone interview, and potential eligible participants will be invited to meet the principal investigator (a physician) at the study site for confirming eligibility based on the following eligibility criteria:

Inclusion criteria include: (1) age ≥ 45 to ≤75 years old; we set the upper age limit to ensure adequate potential for cartilage regeneration [37]; (2) diagnosis of primary knee OA based on clinical and radiological criteria as defined by the American Rheumatology Association [38]; (3) moderate to severe knee pain for at least 3 months, defined as a score of ≥3 (0–6 ordinal response scale) on the question “What is the average level of your left/right knee pain in the past 3 months?”; and (4) failure to achieve pain reduction to a score < 3 (0–6 ordinal response scale) after 6 months of usual care, such as weight reduction, exercise, physical therapy and pharmacological treatment.

Exclusion Criteria include (1) history of corn allergy [39, 40]; (2) previous knee replacement surgery on the referring knee; (3) pregnancy; (4) body mass index (BMI) ≥ 35 kg/m^2^; (5) patients on anti-coagulant therapy; (6) prior knee injections within 3 months; (7) inflammatory or post-infectious knee arthritis, such as clinically diagnosed rheumatoid arthritis, gouty arthritis, psoriatic arthritis and septic arthritis; (8) significant effusion as defined by a ballotable patella; and (9) co-morbidity or lifestyle preventing participation in the study protocol.

### Recruitment and consent

Participants will be recruited in the General Outpatients Clinics (GOPCs) in the New Territories East (NTE) region of Hong Kong. There are seven general outpatient/family medicine clinics in NTE region that provide primary care services for the corresponding population, serving more than 1.2 million people. Subjects with KOA will be recruited via poster advertisement in GOPCs and direct physicians’ referral. The study site is a teaching clinic operated by the Chinese University of Hong Kong. After confirming the eligibility of the participants, the principal investigator will take approximately 15 min to describe the study goals, procedures, activities and possible alternatives, and answers all questions. Following this, interested prospective candidates will be given 7 days to consider the enrolment. The research assistant will then call the candidates for a second visit when written informed consent will be signed. After the enrolment, participants will receive a study identification number and undergo baseline data collection.

### Randomization and Allocation Concealment

Blocked randomization in 1:1 ratio will be used to allocate patients to the two groups [41]. The sequence will be generated by the Random Allocation Software. Random sequence will be concealed using sequentially numbered, opaque sealed envelopes (SNOSE) procedure [42]. These SNOSE will be kept by a person not involved in the care or evaluation of patients, or in the data analysis. The investigator enrolling the patient will have no access to SNOSE. The treatment allocation process starts when the investigator calls the personnel keeping the SNOSE. The computer database is designed in such a way that treatment allocation cannot be changed after randomization. Each participant will receive the SNOSE and they will be asked to sign on it. The SNOSE will only be opened at 52-week.

### Blinding of participants and personnel

Two registered nurses not involved in participant care will prepare the syringes with dextrose or NS identified only by study identification numbers. The syringes will be wrapped in aluminium foil to mask the solutions. The principal investigator and the study coordinator will therefore be blinded to group status of all subjects. The physician who conducts the injections will be blinded to the allocation group; he is also prohibited to communicate with the participants. Dextrose and saline solutions are odorless and identical in color and viscosity. Participants will be blinded to their group status, knowing only their randomization group number. To assess the success of participant blinding, participants will be asked to guess their group status at 12-month before unmasking, and data will be analyzed and interpreted using established procedure [43].

### Blinding in outcome assessment and data analysis process

All data collection will be performed by trained research assistants blinded to the allocation status of the patients via face to face interviews. They will receive rigorous training in standardized data collection procedures. Data entry personnel external to the research team will be employed to perform data entry such that the statistician can analyze data without the need to refer to allocation information, thus ensure blinding.

### Baseline measurement

Demographic data such as age, gender and BMI will be collected. Since objective functional outcome will be evaluated in this trial, the baseline physical activity status will be assessed using the Chinese version of International Physical Activity Questionnaire (IPAQ) [44]. Duration of knee pain and prior knee interventions such as weight reduction, knee exercise, physiotherapy, hyaluronic acid injection, corticosteroid injection or Traditional Chinese Medicine (TCM) etc. will be collected. All other co-morbidities will be documented as potential confounders. The severity of KOA will be graded by radiologist using the Kellgren-Lawrence Grading [45].

### Interventions

Following sterile preparation and injection of 1 ml 1% xylocaine as local anesthetic blebs, participants will be injected under ultrasound guidance with 25-gauge needle directed to the suprapatellar pouch using a linear probe with in plane approach. (Fig. 2) An ultrasound guided approach is used as it can guarantee injection into the joint space [46]. The injection procedures will be conducted under aseptic technique [47]. If both knees are painful, only the more painful knee will be injected. Injections will be conducted at week 0, 4, 8 and 16 for both groups. In case of pain flares after injection, the subsequent injection will be commenced after the flare is subsided, or at 1 month. If participants display allergic symptoms to the injected solution, therapy will be terminated but participants will continue to be followed in their allocated group until the end of the study.

**Fig. 2 Fig2:**
[figure not shown]
Suprapetella pouch injection under USG guidance

Participants in the intervention group will receive injections with loaded syringe containing 5 ml 25% dextrose (D25), prepared by mixing 2.5 ml 50% dextrose with 2.5 ml sterile Water for Injection BP. D25 is a commonly used concentration for intra-articular DPT injection and has been used in previous studies [21, 22]. Participants in the control group will receive injections of 5 ml NS. Recent level one evidence has suggested that NS yields a statistically and clinically meaningful improvement in KOA-related pain up to 6 months after the injection. Therefore, NS will serve as the active control in this trial [48].

Post-injection care: Participants will be observed for 10 min post-intervention consistent with clinical practice and studies [21, 22]. Participants will be advised to take only acetaminophen (500 to 1000 mg every 4 to 6 h as-needed) and avoid non-steroidal anti-inflammatory drugs in the first 48 h after injection, which may interfere with the DPT mechanism of action. They will be allowed to take their usual analgesics medication after 48 h. Participants will be instructed on post-injection care and slow ramp-up of activity. Participants will be contacted 2 days after the injection to assess for side effects.

A home-based post-treatment quadriceps strengthening exercise will be prescribed to both groups and participants will be encouraged to practice daily. Co-interventions will be allowed to both groups, such as conventional medication, physical therapy, acupuncture, herbal medicine, over-the-counter drugs and other active treatments. The use of co-interventions will be retrieved from the Clinical Management System (CMS), an electronic system operated by the Hospital Authority in Hong Kong. Participants will be asked to recall their private treatment as well. However, participants are restricted to receive other injection therapies during the study period.

### Outcome measurement

#### Primary outcome

The Western Ontario McMaster University Osteoarthritis Index (WOMAC) pain score is the primary outcome. WOMAC is a disease-specific quality of life questionnaire for use in osteoarthritis clinical trials [33]. It consists of 24 self-reported items including knee pain (5 items), stiffness (2 items) and function (17 items). The subscales fulfill conventional criteria for content and construct validity, reliability, responsiveness and relative efficiency [49].

#### Secondary outcomes

Secondary outcomes include WOMAC composite score, the WOMAC function and stiffness score. Objective physical function is measured using the 30-s chair stand performance test, 40 m fast-paced walk test and the timed up –and-go test (TUGT). The three tests are recommended by the Osteoarthritis Research Society International (OARSI) as performance-based tests to assess physical function in people diagnosed with KOA [50]. Health related quality of life is assessed using the EuroQuol-5 questionnaire. The measure has strong construct validity, responsiveness and clinometric profile; it has been used to assess the economic impact of OA [35]. Joint pain will also be assessed by the Visual Analogue Score (VAS) in 0–100 mm scale upon walking in the past 48 h. Analgesic consumption will be assessed by the number of participants on analgesics by the 7-day recall diary. Before un-blinding, treatment satisfaction will be tested by asking “Would you recommend the therapy to others with knee OA like yours?”

### Data collection and management

Data will be collected at baseline, and at week 16, 26 and 52. We will record the number of potential candidates, responses received and their resolution, and the number of injection and assessment sessions attended. Follow up data will include the number at each follow up, the number of participants completing the trial, and the number of withdrawals due to all causes. Data entry, transfer and subsequent maintenance will be performed by a data manager. An electronic database will be used, and the server is in a physically secured location with backup on weekly basis. Access to study data is restricted to the study research team by username and password.

### Safety monitoring

Participants have a diary to document any discomfort after each injection; they are advised to call to the study coordinator if they are uncertain whether the discomfort is related to the injections. Standardization forms will be used for monitoring and reporting of side effects and adverse events. The principal investigator will be present in case of a significant adverse event. The principal investigator will report serious adverse events to the ethics committee within 24 h, and annual reports summarizing adverse events will be submitted to the Drug Office of the Department of Health, Hong Kong Administrative Region.

### Statistical issues

#### Sample size Calculation

The sample size calculation is based on 2 RCTs which evaluated the intra-articular injection of DPT and NS for KOA at 6 months [32, 51], assuming their therapeutic effect will remain stable for 1 year. The baseline characteristics of the two trials had comparable age, sex, BMI, and baseline WOMAC score. The mean (Standard Deviation) difference of WOMAC scores at 6 month compared with baseline status was 25.2 (20.3) points for DPT [32], and 9.53 (26.6) points for NS [51], respectively. Thus, assuming a pooled SD of 26.6, a sample size of 34 participants in each arm will have 80% power to detect a significant effect size of 0.70 in a two-sample t-test with alpha set at 0.05. Assuming 10% dropout rate, the total sample size is 76.

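### The planned effect size of 0.70 does not follow from the plan's own inputs (15.67/26.6 = 0.59); with those inputs 34 per arm has about 67% power, not 80%

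*Protocol article*

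**What the plan says.** The section Sample size Calculation of the protocol article relies on two earlier trials, one for each treatment. It gives the mean change in WOMAC score at 6 months, with SD, as "25.2 (20.3) points for DPT [32], and 9.53 (26.6) points for NS [51], respectively", and assumes that the effects persist to one year. The next sentence opens with a word of inference and reads on: "assuming a pooled SD of 26.6, a sample size of 34 participants in each arm will have 80% power to detect a significant effect". The sentence completes the claim with an "effect size of 0.70 in a two-sample t-test with alpha set at 0.05". A 10% dropout allowance then brings the total to 76. The paragraph gives no other difference and no other SD.

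**The concern.** The effect size is presented as the result of the means and SD quoted just before it, yet dividing one by the other gives a clearly smaller value. The SD is also mislabelled. A pooled SD must lie between the two it combines, 20.3 and 26.6, but the figure used equals the larger of them.

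This paragraph is the article's only justification for the number of patients. If the effect size is overstated relative to the inputs, the trial has less power than claimed for the effect its own evidence supports. A null result could then be read as coming from a trial with an 80% chance of finding that effect, when the chance was lower.

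**Working it through.** **Inputs, all from Sample size Calculation unless noted**

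- Dextrose: "25.2 (20.3) points for DPT [32"; saline: "9.53 (26.6) points for NS [51".
- SD used: "assuming a pooled SD of 26.6".
- Target: "to detect a significant effect size of 0.70 in a two-sample t-test", alpha 0.05.
- Claim: "a sample size of 34 participants in each arm will have 80% power".
- Allocation 1:1 (Randomization and Allocation Concealment).
- Sidedness is not stated. I take it as two-sided, because an effect size of 0.70 needs 34 per arm only with a two-sided test; one-sided it would need 26.

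**Step 1: reproduce the plan's figure.** With d = 0.70, two-sided 0.05 and 80% power, the noncentral t calculation gives n = 33.02, rounded up to 34 per arm. Power at 34 is 81.2%. Then 2 × 34 = 68 and 68/0.9 = 75.6, so 76. Everything after the effect size is right.

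**Step 2: derive the effect size from the stated inputs.**

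- Difference: 25.2 − 9.53 = 15.67.
- With the stated SD: d = 15.67/26.6 = 0.589.
- With the two SDs pooled at equal weight: √((20.3² + 26.6²)/2) = 23.66, so d = 15.67/23.66 = 0.662.
- With the simple average of the SDs: (20.3 + 26.6)/2 = 23.45, so d = 0.668.
- With the dextrose SD alone: 15.67/20.3 = 0.772.

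None of these is 0.70. To reach it, the SD would have to be 15.67/0.70 = 22.4, or the difference 0.70 × 26.6 = 18.62 points. Neither figure is stated.

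**Step 3: power at each effect size** (two-sample t-test, noncentral t, two-sided 0.05)

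| SD taken | d | Power, 34/arm | Power, 38/arm | n/arm for 80% |
|---|---|---|---|---|
| 26.6 (as stated) | 0.589 | 66.8% | 71.7% | 47 |
| 23.66 (equal-weight pooled) | 0.662 | 76.8% | 81.3% | 37 |
| 22.4 (implied by 0.70) | 0.70 | 81.2% | 85.3% | 34 |

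The 38-per-arm column assumes no dropout at all.

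A hand check of the first row by the normal approximation: d√(n/2) = 0.589 × √17 = 2.43; 2.43 − 1.96 = 0.47; Φ(0.47) ≈ 0.68. This agrees with 66.8% from the exact t calculation.

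**Step 4: size needed for 80% power at the stated inputs.** 47 per arm is 94 evaluable; 94/0.9 = 104.4, so 105 in total, against 76.

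**Step 5: what 34 per arm can detect with 80% power.** d = 0.690, which at SD 26.6 is 0.690 × 26.6 = 18.3 points.

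**The case against.** The strongest reply is that the document does not show which entry is wrong. The sizes of the two source trials are not given. A weighted pooled SD of 22.4 would give exactly 0.70, with about 70% of the variance weight on the dextrose trial: (26.6² − 22.4²)/(26.6² − 20.3²) ≈ 0.70. In that case 26.6 would be the slip and 80% would be right. This cannot be excluded, but it contradicts the printed SD, so the paragraph needs correcting either way.

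A related reply is that 67% is the least favourable reading, since it applies the saline SD to both arms; the two reported SDs with 1:1 allocation give about 77%. That is fair, and the range should be quoted. The lower figure is nonetheless what the plan's stated SD implies.

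Other defences are weaker:

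- **0.70 as a free-standing target.** The text draws it from the preceding inputs. At SD 26.6 it means 18.62 points, more than the 15.67 the cited trials show.
- **26.6 as a deliberately cautious SD.** Then it should have been used in the effect size, and it was not.
- **A one-sided test.** Power at d = 0.589 would be 77.6%, still below 80%, and 0.70 would need only 26 per arm.
- **A different planned analysis.** The Data analysis section specifies a linear mixed model, whose power may differ. The power claim, however, is made explicitly for a two-sample t-test. What stands is that 67% corrects that calculation and is not an estimate of the mixed model's power.

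**Conclusion.** The concern holds. The stated means and SD give an effect size of 0.59, not 0.70, and the figure called a pooled SD is the saline-arm SD. Taking the stated SD at face value, with a two-sided 0.05 t-test and 34 evaluable per arm, power is 66.8% and the type II error 33% instead of 20%. With the two reported SDs pooled at equal weight, power is 76.8%. Neither reading yields 0.70, and neither gives 80% at 34 per arm. The step from 0.70 to 34 per arm and 76 in total is sound. What remains open is whether 0.70 or 26.6 is the mistaken entry, which only the sponsor can settle.

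**What to change.** Rewrite the paragraph so that its figures agree, leaving the sample size at 76. The sponsor should first establish whether 0.70 or 26.6 was intended, then use one of these forms:

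1. Keep the inputs: difference 15.67, SD 26.6, effect size 0.59, about 67% power at 34 evaluable per arm.
2. Keep 80% power: state that 34 per arm can detect a standardised difference of 0.69, which is 18.3 points at SD 26.6. Label it as the detectable difference, and say that it exceeds the 15.67 points seen in the source trials.
3. If a different pooled SD was really used, print it with the source sample sizes that produce it, and restate the effect size and power from it.

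In every case, stop describing 26.6 as pooled and state that the test is two-sided.

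The cost is one reworded paragraph and, under the first two forms, a less favourable statement of what the trial can detect. No extra patients are required.
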